## Abstract

**Background:**

Deep neck abscesses are a disease in the field of otorhinolaryngology-head and neck surgery that causes significant morbidity, death, and expenditures. Treatment length, whether inpatient or outpatient, is also prolonged. Deep neck abscesses are managed with incision and drainage, abscess exploration, systemic broad-spectrum antibiotic treatment, comorbidity control, and postoperative wound care through recovery. Standard dressings for wound treatment have proven time-consuming and expensive. Honey is one type of dressing that has long been used in wound treatment for a number of body areas and disorders.

**Objective:**

The purpose of this study is to investigate the use of honey as a potential substitute for standard dressings for deep neck abscesses.

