**Methods:**

This is a single-blind randomized controlled trial. Randomization will be done through simple random sampling. The population and sample of the study include all patients with deep neck abscesses treated at [name] Hospital, which is equipped with board-certified otorhinolaryngologists. Patients with deep neck abscesses who were given ethical clearance and meet the inclusion criteria were recruited as study participants until the sample size was reached. There are 18 participants in each group. Participants in the intervention group received standard dressings in addition to honey dressings, whereas those in the control group received standard dressings alone. Proinflammatory cytokines and growth factors, wound size, Bates-Jensen Wound Assessment Tools scoring, and quantitative bacterial colony identification will be all evaluated and assessed. The gathered data will be documented and subjected to statistical analysis.

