**Conclusions:**

We hypothesize that honey may serve as a safe, effective, and affordable alternative wound dressing for the management of deep neck abscesses, with potential benefits in both clinical and health care system outcomes.

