### Goal of the Study

Honey contains antibacterial components that can help treat wound infections, relieve pain, and promote circulation, which all contribute to the healing process. Studies on the use of honey in wound care have primarily been conducted on superficial wounds as well as diabetic ulcers and burns. Previous clinical trials on the use of honey in wound care looked at applying honey to wounds after excision of pilonidal cysts [19]. Research by Rai et al [20] in 2023, which included a randomized controlled trial, compared the use of honey and Edinburgh University’s solution of lime in necrotizing fasciitis wounds. Research by Dubhashi and Sindwani [21] in 2015 looked at the comparative use of honey and phenytoin in chronic wounds. In 2017, Esser [22] examined the use of leptospermum honey on wound healing on the skin of premature newborns admitted to the neonatal intensive care unit. In 2007, Güneş and Eşer [23] compared honey dressings and ethoxy-diamino acridine plus nitrofurazone dressings in patients with decubitus ulcers and assessed healing with the pressure ulcer scale for healing. Wahdini et al [24] reported the use of Madu Nusantara, an Indonesian honey, as a wound dressing for extensive diabetic ulcers in 1 patient with a history of uncontrolled type 2 diabetes mellitus, with good results. Saputri et al [25] from [name] Hospital also reported a case of using Madu Nusantara as a wound dressing in a patient with a submandibular abscess with necrotizing fasciitis. Notably, clinical trials assessing the use of honey on patients with deep neck abscesses have never been conducted before. The mechanistic action of honey in wound healing has been widely hypothesized; however, no one has evaluated its effect clinically, systemically, or on the proinflammatory cytokines and growth factors that play a role in each phase of wound healing.

Thus, this study will conduct a clinical trial of honey as one of the modalities in the treatment of deep neck abscess wounds. Honey is expected to become an alternative dressing material in the treatment of deep neck abscess wounds due to its effectiveness, safety, availability, and affordability compared to standard dressings. Furthermore, honey is readily obtainable at an affordable price; therefore, if the results of wound care using honey are positive, this work will significantly reduce the burden of care on patients, doctors, and hospitals.

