### Recruitment of Participants

This study investigated wound care strategies for patients with deep neck abscesses. The research design used a single-blind randomized controlled trial comparing honey dressings with standard dressings (Prontosan irrigation solution). The study population included patients treated at [name], Yogyakarta. Patient recruitment was conducted from the date of ethical clearance issuance until the required sample size was achieved. Before enrolment, all patients provided written informed consent after being fully informed of the study objectives, procedures, potential risks, and benefits. The study protocol was approved by the Medical and Health Research Ethics Committee, Faculty of Medicine, Public Health and Nursing, Universitas Gadjah Mada, [name] Hospital (KE/FK/0668/EC/2024), ensuring compliance with national and international ethical standards. The inclusion criteria included patients aged older than 18 years with or without comorbidities, except for malignant diseases. The exclusion criteria excluded patients who refused the intervention, underwent vacuum-assisted closure, or had incomplete medical records. Severe allergic reactions to dressings were considered withdrawal criteria. Our findings contribute to the optimization of wound care practices for deep neck abscesses, aiming for improved outcomes and cost-effectiveness. Our investigation was held at the ORL-HNS Department in [name] Hospital.

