### Intervention Procedure

Both the control and intervention groups received wound care following the standard operating procedure established by the Laryngopharyngology Division, ORL-HNS Department, [name] Hospital. This protocol includes wound debridement, saline irrigation, application of gauze rolls, and administration of Prontosan. Necrotic tissue was removed, and the wound was disinfected using sodium chloride before a gauze roll soaked with antibiotic ointment was inserted to serve as drainage. Dressing frequency was determined based on the volume of pus produced—daily dressing was performed until pus production decreased to less than 5 cc, at which point dressings were changed every 3 days, eventually decreasing to once a week when no pus was observed.

In the intervention group, the standard protocol was followed with an additional intervention using Nusantara honey. A 120-cm gauze roll was immersed in 12 cc of Nusantara honey for approximately 1 minute, allowing full absorption before being applied to the wound and covered with sterile gauze. Prontosan gel was used when pus was no longer present to stimulate granulation tissue formation until the wound base reached the surface. Wounds were generally left to heal by secondary intention, unless primary closure or reconstruction was necessary due to extensive tissue loss.

Monitoring of adverse events was conducted directly by the principal investigator and otorhinolaryngology residents during each wound dressing session. If the honey dressing failed to achieve adequate wound healing outcomes, a swab was taken from the wound base for repeat sensitivity culture. The wound care protocol was then reverted to the standard dressing procedure used at [name] Hospital, followed by further management based on the patient’s condition, including the treatment of any comorbidities that might hinder the healing process. The antibiotic protocol applied to both the control and intervention groups included ceftriaxone and metronidazole upon initial presentation, with adjustments made according to the culture results when available. In cases of infection escalation, antibiotics were modified following the hospital’s infection control guidelines. The average wound healing time was 7 days, although some cases required up to a month or additional surgical interventions, such as grafting.

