### Conclusion

In conclusion, this study proposes honey as a potential alternative wound dressing for the management of deep neck abscesses. Based on its established antimicrobial, anti-inflammatory, and wound-healing properties, honey may offer a safe, accessible, and cost-effective solution compared to conventional dressings. If proven effective through this trial, honey-based dressings could contribute to improved clinical outcomes and reduced health care burdens, particularly in low-resource settings.

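### The article presents honey as a substitute for, and affordable alternative to, standard dressing, but the trial compares standard dressing plus honey with standard dressing alone

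*Protocol article*

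**What the plan says.** The question is worded as replacement in several places of the Protocol article:

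- Abstract, Objective: the purpose is to "investigate the use of honey as a potential substitute for standard dressings for deep neck abscesses".
- Abstract, Conclusions: the hypothesis is that "honey may serve as a safe, effective, and affordable alternative wound dressing for the management of deep neck abscesses".
- Goal of the Study: honey is expected to become an alternative material "due to its effectiveness, safety, availability, and affordability compared to standard dressings".
- Recruitment of Participants: the design is described as "comparing honey dressings with standard dressings (Prontosan irrigation solution").
- Discussion, Conclusion: "this study proposes honey as a potential alternative wound dressing for the management of deep neck abscesses", and "honey may offer a safe, accessible, and cost-effective solution compared to conventional dressings".

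The arms are defined as an add-on comparison in three places:

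- Abstract, Methods: "Participants in the intervention group received standard dressings in addition to honey dressings, whereas those in the control group received standard dressings alone".
- Randomization: control is the standard dressing, and intervention is the standard dressing with Nusantara honey added.
- Intervention Procedure: both groups follow the department's standard procedure (debridement, saline, gauze rolls, Prontosan), and "In the intervention group, the standard protocol was followed with an additional intervention using Nusantara honey".

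Measurements, Table 1 and Outcomes list colony counts, wound size, BWAT, cytokines, a growth factor, and clinical and laboratory monitoring. None of them lists cost, dressing consumption or another measure of resource use. The Discussion (under Anticipated Findings) names cost-effectiveness as a topic for future research.

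**The concern.** The stated objective and the randomized contrast are two different questions. Whether honey can take the place of standard dressing needs patients who are treated with honey and without the standard dressing. Whether honey helps when added to standard dressing needs only the two arms described here. The article asks the first and tests the second, and its Recruitment of Participants section describes the comparison in a way that conflicts with three other sections.

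This matters for how a result is read. If the honey arm does better, the data support adding honey to the standard protocol. A reader guided by the objective and conclusions could take the same result as support for leaving the standard dressing out, or for a saving. The first is a regimen that no participant was assigned to, and the second is a quantity that no listed outcome measures.

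**Working it through.** **1. The plan's own figure.** Sample Size gives a control mean of 0.266 cm, SD 1.183 cm, an expected honey mean of 1.433 cm, Zα = 1.64 and Zβ = 1.28. The difference is 1.433 − 0.266 = 1.167 cm, and

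n per group = 2 × [(1.64 + 1.28) × 1.183 / 1.167]² = 17.52, rounded up to 18.

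The stated 18 per group (36 in total) reproduces as a superiority calculation. The point here does not depend on it.

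**2. What the randomized contrast estimates.** Write S for the standard protocol and H for honey, and μ for the mean outcome under each regimen.

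- Arms as defined in Abstract Methods, Randomization and Intervention Procedure: S + H (18 patients) and S (18 patients).
- Estimated: A = μ(S+H) − μ(S), the effect of adding honey.
- Implied by the word substitute: B = μ(H) − μ(S), the effect of honey instead of standard dressing.

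The two are linked by

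B = A − [μ(S+H) − μ(H)].

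The bracket is what the standard protocol contributes in a wound already dressed with honey. Estimating it needs μ(H), and the number of participants assigned to H without S is 0 of 36. B is therefore not identified, whatever the sample size or the result for A.

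**3. What the ambiguity in Intervention Procedure changes.** Three details leave the add-on contrast itself unclear:

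- A roll soaked with antibiotic ointment belongs to the shared procedure, and a honey-soaked roll appears in the intervention paragraph. Whether the second joins or replaces the first is not stated.
- Prontosan gel once pus has cleared is described only in the intervention paragraph.
- After failure of honey, care goes back to the standard procedure, which can be read as meaning that the honey arm had departed from it.

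Split S into the ointment roll O and the remainder P, which includes Prontosan. If the honey roll replaces the ointment roll, the contrast is μ(P+H) − μ(P+O), a swap of one component. If the gel G were used in the honey arm only, the contrast would be μ(S+H+G) − μ(S), and the effect could not be credited to honey alone. In each case Prontosan stays in the shared protocol, so replacement of the standard dressing remains untested.

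**4. Cost.** The claims are affordability (Abstract Conclusions, Goal of the Study) and cost-effectiveness (Discussion, Conclusion). The matching outcomes in Measurements, Table 1 and Outcomes number zero, and the Discussion defers cost-effectiveness. The article's own text therefore places these claims outside the trial.

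**The case against.** The strongest reply is that this is framing and not a fault in the design. The add-on arms are stated three times, once in the Abstract directly after the objective, so an attentive reader can see what was compared. Elsewhere the article calls honey a wound care modality, which fits an add-on trial. The conclusions are hedged as hypotheses and possibilities, no results are reported, and cost-effectiveness is explicitly left to future work. Randomization, sample size and analysis are unaffected.

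Much of this stands. The design needs no change, and the deferral of cost-effectiveness deserves credit. But the hedges concern whether honey works, not which contrast is being tested, and the Objective is a statement of purpose, not a speculation. The deferral also sits beside a Conclusion that offers cost-effectiveness as a possible benefit.

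Some stronger inferences are tempting, and the document does not support them:

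- *The honey arm must cost more per dressing.* This holds only if the honey roll is additional. If it replaces the ointment roll, the sign is unknown, because no prices are given.
- *Savings could come only from fewer dressings.* The Introduction names procedures, surgery, consultation and interdepartmental management as further costs in these patients, so faster healing could save by other routes.
- *The cost of PHMB is the reason for the trial.* The Introduction does call PHMB expensive, but the article never says that Prontosan contains it.
- *The arms differed in gel use.* The sentence after the gel sentence reads as general care, so loose paragraphing is a plausible explanation.

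**Conclusion.** The point holds as a mismatch between the stated question and the tested one. The objective, the comparison wording in Recruitment of Participants, and the hypothesis and conclusions go beyond what the two arms can show. The trial can estimate the incremental effect of adding honey to standard dressing. It gives no direct evidence on substitution (0 of 36 participants assigned to honey without the standard protocol) and, on the outcomes listed, none on affordability or cost-effectiveness.

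This rests on taking the three agreeing descriptions of the arms as what was done, and on the outcome list as printed. A fuller protocol might list more outcomes, but the article's own deferral of cost-effectiveness suggests otherwise. A reader might go further and infer that the trial is invalid or its size wrong. Nothing here supports that: the add-on contrast is a legitimate randomized comparison, and the 18 per group reproduces from the stated inputs.

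**What to change.** 1. Restate the objective, the hypothesis and the design sentence in Recruitment of Participants as honey added to standard dressing versus standard dressing alone, in line with Abstract Methods, Randomization and Intervention Procedure.
2. Do not draw conclusions on substitution, affordability or cost-effectiveness from this trial. Where these ideas are kept, in Goal of the Study and both conclusions, label them as questions for future research, as the Discussion already does for cost-effectiveness. A substitution claim would need a trial with an arm that omits the standard dressing.
3. Reconcile within Intervention Procedure whether the honey-soaked roll joined or replaced the antibiotic-ointment roll, and whether Prontosan gel was used in both arms. If the arms differed in either, describe the contrast as the whole package and not as honey alone.

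The cost is wording only. Recruitment is complete and analysis is under way, so the design is fixed, but the results paper, expected in early 2026 according to the article, can still carry the narrower claim. No data, sample size or analysis changes.

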**Methods:**

This is a single-blind randomized controlled trial. Randomization will be done through simple random sampling. The population and sample of the study include all patients with deep neck abscesses treated at [name] Hospital, which is equipped with board-certified otorhinolaryngologists. Patients with deep neck abscesses who were given ethical clearance and meet the inclusion criteria were recruited as study participants until the sample size was reached. There are 18 participants in each group. Participants in the intervention group received standard dressings in addition to honey dressings, whereas those in the control group received standard dressings alone. Proinflammatory cytokines and growth factors, wound size, Bates-Jensen Wound Assessment Tools scoring, and quantitative bacterial colony identification will be all evaluated and assessed. The gathered data will be documented and subjected to statistical analysis.

**Results:**

This manuscript presents a study protocol for a randomized controlled trial investigating honey as a wound care modality in patients with deep neck space abscesses. Ethical approval and partial funding for the study were obtained in May 2024. Recruitment and data collection commenced in June 2024 and were successfully completed as of June 2025.

**Conclusions:**

We hypothesize that honey may serve as a safe, effective, and affordable alternative wound dressing for the management of deep neck abscesses, with potential benefits in both clinical and health care system outcomes.

**Trial Registration:**

ClinicalTrials.gov NCT06562257; https://clinicaltrials.gov/study/NCT06562257.

**International Registered Report Identifier (IRRID):**

DERR1-10.2196/75475

## Introduction

### Background

The condition known as deep neck space infection (DNSI) emerges when an infection spreads into the deep neck spaces. If left undiagnosed and improperly treated, this condition may become life-threatening [1]. In Spain, there were 9-15 DNSI cases for every 100,000 people in 2012 [2]. DNSI has a 10% to 20% incidence rate and can lead to life-threatening complications if there is excessive accumulation of fluid in the deep neck space. It can also worsen into a deep neck abscess [3]. In Taiwan, there were 196 cases of DNSI between 1996 and 2002, with 33 cases per year, with a mortality rate of 7.6% [4]. DNSI cases increased from 1 case in 2006 to 15 cases in 2015 in Scotland [5]. Meanwhile, from 2004 to 2015, deep neck abscesses had a mortality rate of 1.4% and a complication rate of 22% in Finland [6]. The prevalence is higher in low- and middle-income countries, such as in Mexico, where DNSI has a prevalence of 42 cases over 5 years, with an average of 8.4 cases per year and a mortality rate of 8% [7], and in Ghana, where the prevalence is 135 cases over 7 years (2013-2020) with a mortality rate of 12.6% [8].

Between January 2017 and June 2020, the Otorhinolaryngology-Head and Neck Surgery (ORL-HNS) Department of [name] in Indonesia had the highest number of DNSI cases (24) and the lowest number (8) per semester. With an average rate of mortality of 15% between 2018 and 2020, this number has been rising annually. For instance, in 2021, there were up to 41 patients with DNSI; in 2022, the total spiked to 63 patients; and in November 2023, there were 50 patients [9]. This mortality rate is comparatively greater than that of Bandung and other countries [9]. The average mortality rate was 12.4% from 2015 to 2019 [9]. According to all of the prior studies, men are more frequently affected than women, and while the age range varies from early childhood to adults, the majority of patients are adults.

A deep neck space abscess (DNSA) is an abscess that establishes within the space between the deep neck fasciae. The rapid progression of tonsillar and pharyngeal infections brought on 70% of DNSIs prior to the invention of antibiotics, which frequently led to parapharyngeal abscesses. Infections in adults generally are of dental or odontogenic origin; however, tonsillar infections remain the most common cause in young adults. Although the prevalence and mortality of DNSIs have significantly decreased due to antibiotics, hospital cases of these infections are still frequent [10-12].

Incisional drainage, abscess exploration, systemic broad-spectrum antibiotic therapy, comorbid factor control, and postoperative wound care until the wound closes are the methods used to treat DNSAs. Because a DNSA is situated between the fasciae, the wound has a deeper shape and location and heals at a different rate than other wounds. After DNSA investigation, the wound typically takes a long time to heal due to the complicated nature of treatment methods; the longest healing period can be up to 4 months, with an average of 14 days before the wound closes [13]. In addition to supplementary costs like medical procedures, surgery, consultation, and interdepartmental management, patients with DNSAs endure a significant health cost burden as a result of this prolonged wound healing.

A wound is defined as any discontinuity, disturbance, or disruption in the anatomical structure of the skin or connective tissue that results in functional impairment [14]. The wound healing process is divided into several stages, including homeostasis, inflammation, proliferation, and remodeling. These stages are modified by diverse cellular contacts and controlled by the secretion of local chemical signals [14].

The recovery process of a wound determines whether it is acute or chronic. The Centers for Disease Control and Prevention divides wounds into 4 classifications: clean, clean contaminated, contaminated, and dirty or infected. Postdrainage and abscess exploration wounds are dirty or infected open deep wounds that will heal through secondary wound healing.

In acute conditions, most surgeons continue to use sterile gauze with saline as the wound dressing of choice [15]. The wound irrigation solutions used include normal saline, tap water, povidone-iodine, Ringer lactate solution, hypochlorous acid, polyhexamethylene biguanide (PHMB), sodium hypochlorite, and electrolyzed strong water acid. Although these solutions can be used as wound irrigation agents, only some of them have antibacterial activity. One of the bactericidal wound irrigation agents is PHMB, an antimicrobial polymer that is effective against intracellular and biofilm forms of *Staphylococcus aureus* [16]. PHMB is quite effective in the treatment of wounds in deep neck abscesses. However, the unit cost is relatively high and is frequently not covered by government insurance.

Wound dressings with honey have been practically used since ancient Egyptian times to treat abscesses, diabetes mellitus, eye and ear infections, gastrointestinal diseases, oral ulcers, gynecological diseases, nail infections, airway infections, and wounds after circumcision [17]. Honey has also been used since the wartime era of the Prophet Muhammad to treat wounds. It was later shown that honey can kill bacteria in wounds and can be used as a medicine. This method is still used today in several Islamic countries to heal wounds and has been used by Russian soldiers since World War I to prevent wound infection and accelerate wound healing [18].

Honey has a high sugar content and high acidity, which can reduce bacterial growth. It also contains hydrogen peroxide, which is capable of eradicating pathogenic microbes, as well as antibacterial chemical compounds. Honey is more readily obtainable and less expensive than other dressing materials.

